**Methods:**

In this single-center, double-blind, randomized controlled trial, 60 older adults with insomnia and subjective cognitive decline will be recruited and randomly assigned to the KGT or placebo group. The KGT group will take KGT granules thrice a day for 12 weeks, whereas the control group will take placebo granules in the same manner.

Participants will be assessed for sleep, cognitive function, quality of life, and depression using the Pittsburgh Sleep Quality Index-Korean (PSQI-K), Insomnia Severity Index-Korean (ISI-K), Seoul Neuropsychological Screening Battery–Dement (SNSB-D), 36-item MOS Short Form Survey (SF-36) and Short version of the Geriatric Depression Scale (S-GDS) before and at the end of administration of the investigational product. The PSQI-K, ISI-K, and SF-36 will be further assessed 12 weeks after the end of medication to determine whether the effects on sleep and quality of life are sustained. The PSQI-K total score difference between the two groups at 12 and 24 weeks will be the primary outcome; all other endpoints will be secondary.

Safety will be assessed by performing blood tests and electrocardiograms before taking the investigational drug, 6 weeks after taking the drug, and 12 weeks after taking the drug; any adverse events will be observed throughout the study.

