### Intervention

KGT or placebo granules (one dose: 3.0 g) are orally administered with water 3 times a day (30 min after meals) for 12 weeks. KGT is a herbal medicine approved by the Ministry of Food and Drug Safety and is manufactured by Kyoung Bang Pharmaceutical Co., Ltd. (Incheon, Republic of Korea). It is yellow-brown granules and consists of *Astragali Radix* 1.0 g, *Ginseng Radix* 1.0 g, *Atratylodis Rhizoma* 1.0 g, *Poria* 1.0 g, *Zizyphi Fructus* 0.67 g, *Zingiberis Rhizoma* 0.33 g, *Saussureae Radix* 0.33 g, *Glycyrrhizae Radix* 0.33 g, *Zizyphi Spinosi Semen* 1.0 g, *Longan Arillus* 1.0 g, *Angelicae Radix* 0.67 g, *Polygalae Radix* 0.67 g, *Bupleuri Radix* 1.0 g, *Moutan Radicis Cortex* 0.67 g, and *Gardeniae Fructus* 0.67 g. The placebo was manufactured at the National Institute for Korean Medicine Development (NIKOM) Herbal Medicine Production Center (GMP) in Daegu, Republic of Korea, with an appearance, taste, and smell similar to KGT.

The participants will be trained to take the drug three times a day and then return the remaining medication at their next visit. Regarding compliance with the investigational drug, the remaining drug brought in by the participant at the time of the next visit is identified and recorded on a case report form. Medication compliance (%) signifies that the participant’s actual dose is divided by the number of investigational drugs taken by the date of the participant’s visit based on the date of the last visit × 100. The actual dose is the number of returned drugs on the day of the participant’s visit, subtracted from the drugs provided to the participant. When visiting 6 weeks after taking the drugs, the investigator retrieves the unused dose and reversely check the total dose. If medication compliance is less than 60% at the 6th week of taking, the subject will drop out. Even if all doses were administered over the next 6 weeks, the final medication compliance is < 80%. The final medication compliance must be 80% or higher; if medication compliance is less than 80%, the participant is excluded from the per-protocol (PP) analysis group.

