### Primary outcome

#### PSQI-K

The Pittsburgh Sleep Quality Index (PSQI) is a subjective evaluation tool for sleep quality that includes quantity, depth, and peace of sleep. Subjective sleep quality, sleep latency, sleep duration, sleep efficiency, sleep disturbance, sleep medication use, and daytime dysfunction are evaluated. Each domain has a minimum score of 0–3 points, and the total score of the seven subdomains ranges from 0 to 21 points [31]. The higher the total score, the higher the severity of the sleep disorder; if it exceeds 5 points, it is judged as a sleep disorder. In this study, the Korean version will be used that has been independently confirmed for validity and reliability [24].

The primary outcome is the difference between the treatment and placebo groups in terms of changes in the total PSQI-K score observed before taking the investigational drug, at the end of 12 weeks of medication, and after 12 weeks of 12-week medication.

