### Statistical analysis

All statistical analyses is a two-sided and the significance level is set at 5%. Statistical program SPSS (Ver 25.0 or more updated, IBM Corporation) will be used as the primary analysis tool. All participants randomized according to the intent-to-treat (ITT) analysis principle are considered as the Full Analysis Set (FAS). Participants who have completed taking investigational product for 12 weeks and completed up to the follow-up period (week 24) after 12 weeks are referred to as the protocol compliance analysis group, as per-protocol (PP).

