#### Efficacy analysis

Efficacy evaluation is based on the FAS analysis group, and efficacy is analyzed and presented with reference to the PP analysis group. For safety evaluation, the ITT analysis group is the main assay.

Analysis of primary efficacy endpoints.

Participants with PSQI-K scores before the study and at least once after consuming the investigational product are analyzed. Based on the baseline, the difference between the two groups in the total PSQI-K score change at weeks 12 and 24 is analyzed using repeated measures analysis of variance (RM ANOVA) and linear mixed model (LMM) methods.

2)Analysis of secondary endpoints.

The PSQI-K score change will be analyzed by a paired t-test within each group for changes at 12 and 24 weeks based on the baseline. The ISI-K score change will be analyzed using the paired t-test within each group and the independent t-test between the two groups at the 12-week dosing period and at 24 weeks based on the baseline. The SNSB-D and S-GDS score changes will be analyzed using the paired t-test within each group and the independent t-test between the two groups with respect to the score change at week 12, based on the baseline. The SF-36 score change will be analyzed using a paired t-test within each group and an independent t-test between the two groups at 12 and 24 weeks based on the baseline. Changes over time will be analyzed using the RM ANOVA and LMM methods. The estimated values of the mean difference between the groups, 95% confidence intervals, and p-values will be presented.

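### The primary PSQI-K outcome gives weeks 12 and 24 equal status and assigns two unranked methods, without saying which week, model or contrast decides

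*Protocol article*

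**What the plan says.** The abstract states: "The PSQI-K total score difference between the two groups at 12 and 24 weeks will be the primary outcome". The Primary outcome section agrees: "The primary outcome is the difference between the treatment and placebo groups in terms of changes in the total PSQI-K score", observed before dosing, at week 12 and 12 weeks after dosing ends. Study design names the same three occasions. In Efficacy analysis, with baseline as the reference, "the difference between the two groups in the total PSQI-K score change at weeks 12 and 24 is analyzed", and this is done "using repeated measures analysis of variance (RM ANOVA) and linear mixed model (LMM) methods". The two methods are joined by a plain conjunction, and neither is ranked.

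The Statistical analysis section adds: "All statistical analyses is a two-sided and the significance level is set at 5" per cent. The level is not divided between weeks or methods.

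Two statements show that the weeks differ in kind. Under Intervention, "KGT or placebo granules (one dose: 3.0 g) are orally administered with water 3 times a day (30 min after meals) for 12 weeks", so week 12 is the end of treatment and week 24 is off drug. The abstract gives the later PSQI-K measurement a follow-on purpose: "to determine whether the effects on sleep and quality of life are sustained".

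**The concern.** Week 12 asks whether KGT works by the end of treatment. Week 24 asks whether an effect outlasts treatment. The article makes both primary on equal terms but does not say whether success needs week 12, week 24, either, both, or a joint test. Nor does it say which of the two models supplies the answer.

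Whether the 5% level applies to the primary claim, and what a significant result would mean, therefore depend on a choice still open. If that choice is made after the data are seen, a favourable week or model can be presented as the primary result. If an averaged test is used, a real end-of-treatment effect that fades can be missed.

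**Working it through.** **Inputs from the article.** 30 per group (Sample size); 1:1 allocation; two-sided 5%; PSQI-K at baseline, week 12 and week 24. The only figure to reproduce is the 5% level. The article gives no effect size, SD, power or correlation, so those below are assumptions.

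**Assumptions.** Normal scores and complete data. SD of change 3.5 at each week. True week-12 effect 2.6 points. Correlation *r* between the two change scores 0.3 to 0.7. Simulations use 30 per arm, with 40,000 null trials and 20,000 per power scenario. They assume equal correlation between visits (which makes *r* = 0.5) unless stated.

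**Step 1: one pre-specified test.** Each candidate test used alone (week 12, week 24, averaged change, joint group-by-time) rejects in about 5% of null trials. The stated level is reproduced whenever one test decides.

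**Step 2: either week may decide.** P(either) = 0.05 + 0.05 − P(both), where P(both) comes from the bivariate normal distribution.

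| *r* | P(both) | P(either) |
|---|---|---|
| 0 | 0.0025 | 9.75% |
| 0.3 | 0.0049 | 9.5% |
| 0.5 | 0.0093 | 9.1% |
| 0.7 | 0.0165 | 8.4% |

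Simulation gives 8.4% to 9.2% for *r* of about 0.4 to 0.7.

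**Step 3: what the two methods add.** Take the joint group-by-time test from RM ANOVA, and an unstructured two-degree-of-freedom test standing in for the mixed model. Accepting whichever is significant gives 5.6% to 5.9% under equal visit correlation, so the methods alone add less than 1 point. Adding both of these to the either-week rule gives about 10%, and adding the averaged-change test as well gives about 11%.

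**Step 4: one averaged group effect decides.** Let *f* be the fraction of the week-12 effect remaining at week 24. The averaged effect is 2.6(1 + *f*)/2, with SD 3.5√((1 + *r*)/2) and standard error SD × √(2/30).

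- Week 12 alone: standard error 3.5 × 0.258 = 0.904; 2.6/0.904 = 2.88; power 81% (noncentral t, 58 df).
- Averaged, *r* = 0.5, *f* = 0: effect 1.3; SD 3.03; standard error 0.783; ratio 1.66; power 37%. At *r* = 0.3 it is 42%, and at *r* = 0.7 it is 33.5%.
- Averaged, *r* = 0.5, *f* = 0.5: 69%.
- Averaged, *r* = 0.5, *f* = 1: 90% to 91%, above week 12 alone.

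**Step 5: the joint group-by-time test decides.** In the same setting, alpha is about 5%. Power is about 84%, 72% and 85% for no, half and full persistence. The test has no direction in time, so a significant result does not locate the difference at week 12 or week 24.

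**Step 6: dropout.** Efficacy analysis admits participants with a baseline score and at least one post-dose score. Standard RM ANOVA over three visits keeps only those with all three, whereas a mixed model keeps everyone admitted. With dropout, the two named methods analyse different people, and RM ANOVA does not match the stated population.

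**The case against.** The strongest reply is that the article describes one repeated-measures analysis, not separate weekly tests. Where Efficacy analysis wants week-by-week group comparisons it names independent t-tests, as for ISI-K and SF-36, and it names none for PSQI-K. A joint group-by-time test over the three measurements is a common use of both methods. By Step 5 it neither inflates alpha nor loses much power when the effect fades. This stands. A reader might infer that the 5% level is simply broken, but the article states no either-week rule, and a joint test or a both-weeks rule would keep the level at or below 5%.

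Two larger figures are also tempting and should not be used. Power of about 20% for a fading effect arises only if the deciding test is a group main effect on raw scores with baseline averaged in; Efficacy analysis speaks of change from baseline. A false-positive rate of 12% to 13% arises only by counting further routes, including a week-12-versus-week-24 comparison that does not by itself show efficacy.

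Finally, covariance structure and model details commonly belong to an analysis plan that is not shown, and their absence is no fault. But the deciding time point is part of the definition of the primary outcome. The article does not leave it open by silence: it fixes two weeks and two methods as equals, consistently across the abstract, design, outcome and analysis sections.

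**Conclusion.** The point holds in conditional form: the primary claim has no single stated decision at 5%.

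- **Either week decides:** about 9% false positives, or about 10% to 11% with the model open too.
- **An averaged effect decides:** 5%, but power of roughly 33% to 42% instead of about 80% for an effect gone by week 24.
- **The joint test decides:** 5% with good power, but no answer as to which week.

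The two time points drive the problem. The two methods matter little with complete data and more with dropout. The false-positive rates rest on assumed correlations and normality. The power figures rest also on the assumed 2.6 points and SD of 3.5, neither of which comes from the article. The article does not show that a favourable week will be selected, only that nothing in it prevents this.

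**What to change.** Name one deciding analysis before unblinding. For example:

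> *The primary comparison is the KGT–placebo difference in PSQI-K change at week 12, estimated from one linear mixed model with week as a category, two-sided 5%. The week-24 contrast from the same model is tested at 5% only if week 12 is significant, and answers whether the effect is sustained. RM ANOVA is a sensitivity analysis.*

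This keeps 5% without splitting it and matches the purpose the abstract gives the later measurement. Bring the abstract, Study design, Primary outcome and Efficacy analysis into line, and check the registry entry, which is not available here.

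Other rules would also hold the level: a named joint test, both weeks required, or 2.5% at each week. The last keeps the overall level at 4.94% if the tests are independent (1 − 0.975²). By the normal approximation, it cuts power from 80% to 71% at the standardised difference of 0.723 that 30 per arm detects with 80% power at 5%.

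The cost is wording, with no added participants or procedures. Two things are given up under the example: a week-24-only difference can no longer be claimed as primary, and some power is lost against an averaged test if the effect fully persists (about 81% against 91%). Eight participants had been enrolled by 25 August 2023, with recruitment planned to October 2024. Current status is not known, so the condition that matters is that the change is dated before unblinding.

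### The primary PSQI-K endpoint has two visits and two unranked methods at an unadjusted 5% and no deciding rule, so 5% is not guaranteed for the primary conclusion

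*Protocol article*

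**What the plan says.** All places are in the protocol article.

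- **Two visits.** The abstract states: "The PSQI-K total score difference between the two groups at 12 and 24 weeks will be the primary outcome". The Primary outcome section agrees: "The primary outcome is the difference between the treatment and placebo groups in terms of changes in the total PSQI-K score observed before taking" the drug, at the end of the 12 weeks of dosing, and 12 weeks after that. The Efficacy analysis section again names "the difference between the two groups in the total PSQI-K score change at weeks 12 and 24".
- **Two methods.** The same sentence of the Efficacy analysis section says this difference "is analyzed using repeated measures analysis of variance (RM ANOVA) and linear mixed model (LMM) methods". The two are joined by a plain conjunction, with no order.
- **Significance level.** The Statistical analysis section says "All statistical analyses is a two-sided and the significance level is set at 5" per cent. No division or adjustment is given for the primary endpoint.
- **Who is analysed.** "Participants with PSQI-K scores before the study and at least once after consuming the investigational product are analyzed".
- **Populations are ranked.** "Efficacy evaluation is based on the FAS analysis group, and efficacy is analyzed and presented with reference to the PP analysis group". The choice between FAS and PP is therefore settled and adds nothing to the problem.
- **Purpose of the follow-up visit.** The abstract says the later assessment is "to determine whether the effects on sleep and quality of life are sustained".

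**The concern.** A primary endpoint needs one rule that turns the data into a yes or a no. Here the text fixes two visits and two methods and stops. It does not say which visit decides, whether one or both must be significant, which method prevails if they disagree, or which model effect is the test. A claim could then rest on whichever visit or method falls below 0.05, and that choice could be made after the results are known.

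The two methods need not even analyse the same people. Standard RM ANOVA uses only participants with every visit, whereas the inclusion rule for the primary analysis accepts a baseline and a single post-dose score, which suits the LMM. Missing week-24 scores are plausible: the Drop-out criteria remove participants for low compliance at week 6 or week 12, for unapproved drugs that may affect the results, and for loss to follow-up. The more week-24 scores are missing, the further the two methods can diverge.

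**Working it through.** **Inputs from the article.** Two-sided 5% for each analysis (Statistical analysis); two primary visits (Abstract, Primary outcome, Efficacy analysis); two methods (Efficacy analysis); 30 per group (Sample size), allocated 1:1.

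**Assumed, because the article gives no figure.** Correlation of the two changes from baseline, 0 to 0.9; share missing at week 24, 0% or 15%.

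**Step 1: the plan's own 5%.** For one test, 1 − (1 − 0.05) = 0.05. A null simulation (30 per arm, 20,000 trials per scenario, LMM approximated by an unstructured-covariance likelihood) gave 4.6% to 5.4% for each candidate test taken alone. The stated level is correct for each analysis.

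**Step 2: success at either visit, one method.** With independent tests, 1 − 0.95² = 0.0975. With correlation r between the two test statistics, the error is 1 − P(|Z₁| < 1.96 and |Z₂| < 1.96) for a bivariate normal pair. The error if both visits must be significant, with no effect at either, is 0.05 + 0.05 minus that figure.

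| r | either visit | both visits |
|---|---|---|
| 0 | 9.75% | 0.25% |
| 0.3 | 9.51% | 0.49% |
| 0.5 | 9.07% | 0.93% |
| 0.7 | 8.35% | 1.65% |
| 0.9 | 7.04% | 2.96% |

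The r that matters is that of the changes, not of the raw scores. If the three scores are equally correlated at ρ with equal variances, the changes share the baseline and their correlation is (1 − ρ)/[2(1 − ρ)] = 0.5 whatever ρ is. That gives 9.07%. The simulation gave 8.6% to 9.2% for the either-visit rule.

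**Step 3: the choice of method as well.** Simulated ranges:

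| What counts as success | error |
|---|---|
| One joint test over both visits, one method | about 5% |
| Joint test, either method | 5.6% to 6.9% |
| Group-by-time or group effect | 7.1% to 7.7% |
| Either visit, either method, complete data | 8.9% to 9.3% |
| Either visit, either method, 15% missing week 24 | 11.0% to 11.3% |

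With complete data the second method adds almost nothing to the either-visit error. It adds about two percentage points once participants are missing at week 24, because RM ANOVA and the LMM then use different data.

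**Step 4: after a repair.** One named test gives 5.0%. Each visit at 2.5% gives 1 − 0.975² = 4.94% if independent, and never more than 5%. Week 12 at 5%, then week 24 at 5% only if week 12 succeeds, also keeps the overall error at or below 5%.

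**The case against.** The best defence is that the 5% is stated for each analysis and each analysis delivers it. Two visits do not imply two tests. With baseline, week 12 and week 24 as the levels of time, the group-by-time test is one two-degree-of-freedom test of exactly the two differences in change, at about 5%. Requiring both visits is stricter still. No passage says that either visit, or either method, suffices. The model effect, covariance structure and handling of missing data are commonly left to an analysis plan that is not shown. Most of this stands: it shows that 5% could be met. It does not show that it will be, because the article fixes two visits and two methods and ranks neither, although it does rank the populations.

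Three stronger readings are tempting and are not supported.

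- **That the 5% level is broken outright.** A reader might infer this, but the excess arises only under an either-visit, either-method or either-effect rule, and the article states none of these.
- **That the error reaches 13% to 14%.** This requires adding an averaged-effect test and an interaction test to the two visit tests. The article designates no such family.
- **That a benefit fading after dosing is badly diluted.** Take an assumed effect of 0.736 SD at week 12 (80% power, 30 per arm) that is gone by week 24. A test of the two-visit average has an effect of 0.736/2/√((1 + r)/2), which is 0.46, 0.42 and 0.40 at r = 0.3, 0.5 and 0.7, and power of 41%, 37% and 33%. The article never names that averaged test. A joint two-degree-of-freedom test has 74%, 83% and 95% power in the same cases.

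On partial data, the LMM named in the same sentence does satisfy the one-post-dose-score rule. The conflict is therefore a reason to rank the methods, not to remove RM ANOVA everywhere.

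**Conclusion.** The point holds as an undefined decision rule for the primary conclusion, not as a proven breach of 5%. Across readings the article leaves open, the error with no effect at either visit runs from 0.25% (both visits required, independent changes) to about 11% (either visit, either method). The either-visit reading alone gives about 7% to 10%. These figures rest on an assumed correlation of the changes between 0.9 and 0; the 11% also needs an assumed 15% missing at week 24. The mismatch between standard RM ANOVA and the inclusion rule for partial data needs no assumption about correlation, and takes effect as soon as anyone misses a visit.

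**What to change.** Before unblinding, amend the primary analysis in three respects.

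1. Name the LMM as the single primary method. It matches the rule that a baseline and one post-dose score are enough.
2. Make RM ANOVA a sensitivity analysis for the primary endpoint. It may stay among the secondary analyses of change over time, where it does not affect the primary error.
3. State one decision rule from the LMM. For example, test the treatment difference in PSQI-K change at week 12 at two-sided 5%, and test week 24 at 5% only if week 12 is significant. This fits the abstract's aim of seeing whether effects last.

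The sequential rule is one valid choice among several. A joint test of both visits, or 2.5% per visit, also controls the error and keeps the two visits on an equal footing, closer to how the primary outcome is now worded.

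The cost is a short wording change; the Trial status section reports eight participants enrolled as of August 2023. The sequential rule allows no confirmatory week-24 claim if week 12 fails. Splitting the level costs some power: for 80% power with 30 per arm, the normal-approximation detectable effect rises from 0.72 SD at 5% to 0.80 SD at 2.5%.

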### Eligibility

#### Inclusion criteria

Participants who meet all the criteria below are eligible to participate:Those who complain of insomnia according to the criteria presented by DSM-5 > 65 years.Those with an Insomnia Severity Index Korean (ISI-K) score of > 8.Those with a Subjective Cognitive Decline Questionnaire (SCD-Q) score of > 7 and a Korean Dementia Screening Questionnaire-Cognition (KDSQ-C) score of < 6.Those who have not received any new treatments related to insomnia within the last 2 weeks: pharmacological and non-pharmacological treatments.Those who have not received cognitive-related drug treatments within the last 2 weeks.Cognitive-related drugs include cerebral function-improving agents, cerebral circulation-activating drugs, and other drugs or nutrients that can affect cognition.Those who have been in a stable state without any change in medications for underlying diseases for the past 4 weeks or more and who are planning to take stable medications during the study period.Those who have no problems with communication.Those who voluntarily decided to participate and signed the written consent form.

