### Randomization, allocation concealment, and blinding

Sixty participants who meet the criteria will be assigned to the treatment or control group at a ratio of 1:1 by an investigator independent of this clinical study using the block randomization method. A random assignment table is randomly assigned according to a random number table generated using the RAND function in Excel. According to the randomization table, the investigational drug manufacturer packs the treatment drug and placebo in the same manner, labels the serial number in the form of R-00, and provides it to the principal investigator. Registered pharmacists manage the investigational drugs and provide them to the participants according to their randomization number.

To keep the participants blind, the authenticity of the drug will not be disclosed until the end of the study period. The properties of the placebo are the same as those of the treatment drug, as to maintain double blindness. The investigators, coordinators, and pharmacists should remain blind to the assignments until the end of the study period.

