### Secondary outcomes

#### PSQI-K

Changes in the total PSQI-K score observed before taking the investigational drug, at the end of 12 weeks of medication, and after 12 weeks of the 12-week medication in each group.

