### Sample size

The herbal medicine, Kami Guibi-tang (KGT), used in this study is already approved for insomnia by the Korean Food and Drug Administration. This study aimed to evaluate insomnia in older adults and assess cognitive function. According to the central limit theorem, a sample consisting of > 30 individuals per group is assumed to be normally distributed; therefore, the sample size for this study was 30 individuals per group. If the normality test confirms that the distribution is normal, we will perform statistical analysis parametrically [35].

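### Within-arm paired t-tests are planned as efficacy tests for the secondary endpoints, and for secondary PSQI-K they are the only test named; they should be descriptive

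*Protocol article*

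**What the plan says.** Under Statistical analysis, Efficacy analysis, the article assigns a within-arm paired t-test to every secondary endpoint.

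- **Secondary PSQI-K.** The endpoint is defined under Secondary outcomes as "Changes in the total PSQI-K score observed before taking the investigational drug, at the end of 12 weeks of medication" and at week 24, separately for each arm. The named analysis is "The PSQI-K score change will be analyzed by a paired t-test within each group for changes at 12 and 24 weeks". No contrast with placebo is named for this endpoint.
- **ISI-K and SF-36.** Paired t-tests within each arm and independent t-tests between arms, at weeks 12 and 24.
- **SNSB-D and S-GDS.** The same pair of tests, at week 12 only.
- **Primary PSQI-K.** This analysis is between arms: "the difference between the two groups in the total PSQI-K score change at weeks 12 and 24 is analyzed", by repeated measures ANOVA and a linear mixed model.

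The section also promises between-group mean differences with 95% confidence intervals and p-values. On significance, the Statistical analysis section says "All statistical analyses is a two-sided and the significance level is set at 5" per cent. That covers the paired tests, and nothing sets them apart as descriptive.

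**The concern.** A paired t-test in one arm asks whether the mean changed from baseline. It does not ask whether KGT changed it. The design gives several reasons why scores might move without any drug effect:

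- **Regression to the mean.** Entry requires a raised insomnia score: "Those with an Insomnia Severity Index Korean (ISI-K) score of > 8". ISI-K is also an outcome, so the effect is direct there. PSQI-K has no entry threshold, so there it is only indirect, through its correlation with ISI-K.
- **Placebo response.** PSQI-K, ISI-K, SF-36 and S-GDS are self-reports and open to it.
- **Practice.** SNSB-D is given at screening and again at week 12, so some gain from repetition is possible.

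The article does not quantify any of these. The double-blind placebo arm is there to cancel them, and a one-arm test lets them back in. A significant change under KGT, or significance under KGT but not under placebo, could then be reported as a secondary efficacy result although the comparison of the arms shows nothing. No sentence says which test governs if the two disagree.

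**Working it through.** The article states no power, effect size or SD for this point, so there is no figure to reproduce. The check sizes what the paired tests would do if KGT had no effect.

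**Inputs from the article**
- Sample size: "therefore, the sample size for this study was 30 individuals per group" (Sample size section).
- Allocation: "assigned to the treatment or control group at a ratio of 1:1" (Randomization section).
- Two-sided 5% level for all analyses (Statistical analysis section).

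**Assumption.** Both arms improve by the same amount d = mean change / SD of change. The article gives no value, so d is shown as a range.

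**Step 1: chance that one arm's paired test is significant for improvement.** With n = 30 there are 29 degrees of freedom and the critical value is t = 2.045. The test statistic is noncentral t with noncentrality d × √30, and q = P(t > 2.045).

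**Step 2: chance that KGT is significant and placebo is not.** The arms are independent and identical under the assumption, so this is q(1 − q). It cannot exceed 0.25, which it reaches at q = 0.5.

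| d (assumed) | d × √30 | q | q(1 − q) |
|---|---|---|---|
| 0.2 | 1.10 | 0.184 | 0.150 |
| 0.37 | 2.03 | 0.500 | 0.250 |
| 0.5 | 2.74 | 0.754 | 0.186 |
| 0.8 | 4.38 | 0.988 | 0.011 |

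**Step 3: the between-group test in the same situation.** With no KGT effect it keeps its level whatever the common improvement. In simulations at d = 0.2, 0.36, 0.5 and 0.8 (50,000 trials each) it rejected in about 5% of trials, about 2.5% in favour of KGT. The simulations also matched q and q(1 − q).

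**Step 4: an example in PSQI-K points.** Again by assumption, take a common improvement of 1 to 2 points and an SD of change of 3 to 4. The KGT paired test is then significant in 26% (1 point, SD 4) to 94% (2 points, SD 3) of trials. KGT alone is significant in about 5% (2 points, SD 3) to 25% (1.5 points, SD 4).

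**Step 5: why the two kinds of test can disagree.** A within-arm change reaches p < 0.05 once the observed change is 2.045 / √30 = 0.37 SD. The between-group t-test (58 degrees of freedom, critical value 2.002) needs an observed difference of 2.002 × √(2/30) = 0.52 SD. It has 80% power only for a true difference of about 0.74 SD (0.72 by the normal approximation). A significant KGT arm beside a non-significant comparison is therefore plausible.

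**The case against.** The strongest reply is that a between-group comparison is already planned on every scale. PSQI-K change is compared between arms as the primary endpoint, at the same two time points, and the other four instruments each have an independent t-test. This stands and limits the point. A reader might infer that the trial's efficacy case rests on uncontrolled change, and the article does not support that. Outside secondary PSQI-K the paired tests are redundant, not the sole evidence.

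Second, no sentence says that efficacy will be concluded from one arm's p-value, or from significance in one arm only. This also stands. A reader might take the 25% as a false-positive rate of the planned analysis. It is the maximum for a reading that the article permits but does not adopt, and it falls to 1% at d = 0.8.

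Third, the mechanisms are uneven. SCD-Q is used for eligibility only and is not an outcome, so selection on it does not directly bias any listed paired test. ISI-K > 8 is a low cut on a 0 to 28 scale. Placebo response and practice are plausible, but the article does not document them. All of this is accepted. The objection to a one-arm test does not depend on how large each mechanism is.

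Fourth, the sentence on changes over time by repeated measures ANOVA and mixed model might cover PSQI-K as well. It follows the SF-36 sentence and its scope is unclear. Even on the wider reading, the secondary PSQI-K endpoint is still defined per arm, and its named test is still the paired one.

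**Conclusion.** The point holds at secondary level. The article places within-arm paired t-tests under its efficacy heading at the 5% level without a descriptive label, and for secondary PSQI-K it names no other test. These tests cannot show a KGT effect.

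With 30 per arm and no KGT effect, the KGT paired test is significant in 18% to 99% of trials for a common improvement between 0.2 and 0.8 SD of change. KGT alone is significant in 1% to 25%. The matching between-group figure is about 2.5%. The range of d is an assumption, as is the equal improvement in both arms.

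The primary PSQI-K inference is not affected. The practical risk is a null primary comparison reported beside a nominally positive within-arm result on the same scale.

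**What to change.** Relabel all within-arm changes, including the secondary PSQI-K endpoint, as descriptive: mean change with 95% confidence interval, without p-values. Add one sentence saying that efficacy conclusions for every endpoint rest on the between-group difference in change that is already planned, preferably adjusted for baseline. The secondary PSQI-K endpoint need not be deleted; relabelling it is enough.

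The cost is small but goes beyond SAP wording. The endpoint is defined in the protocol, recruitment has begun (eight enrolled as of the Trial status section), and the Discussion says that changes to the study require IRB approval. A minor amendment to the protocol and SAP is therefore needed. The within-arm p-values are lost. Data collection, visits and patients are unaffected.
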